### **5.2.3. Events of interest**

Within the framework of the evaluation of both MD (cord + sheath and adhesive elastic band) the **events of interest** induced by these MDs will be collected.

These are:

- Self-extubations
- Laryngotracheal dyspnea
- Ventilator-associated pneumonia

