| Collection of re-intubations                                                                        | X  | X  | X  | X  | X  | X  | X  | X  | X  | X  | X   | X          | X   |
| Collection of adverse events related to the investigation procedure and incidents related to the MD | X  | X  | X  | X  | X  | X  | X  | X  | X  | X  | X   | X          | X   |

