### 5.2.2. Adverse events / Expected incidents

- List of Incidents/Expected Events related to the investigational medical device/comparator

- *The medical device under study (elastic adhesive tape):*

The MD is used in its indication: fixation.

(There is no detailed AE in the technical data sheet except for one contraindication: subjects sensitized to synthetic products).

Expected Incidents / AE:

- Intolerance to synthetic products
- Skin lesions and mucosal lesions in the path of fixation. (*13% of patients according to reference 7*)
- Loss of adhesiveness of the tape.

- *The medical device comparator (cord + sheath):*

The comparator is used in its indication: fixation.  
There are no AE detailed in the technical data sheet.

Expected Incidents / AE:

- Skin and mucosal lesions in the path of fixation (*43% of patients in reference 7*)
- Shearing, potential cut due to cord.

- List of expected AEs related to investigative procedures:

- *Medical device implementation:*

- Unscheduled extubations: self-extubations and accidental extubations during care (*7 to 16% of patients depending on reference 17*)
- Tracheal complications including laryngeal dyspnea
- Ventilator-associated pneumonia.

- List of expected AEs related to other additional procedures:

- *Auxiliary Drugs/MDs:*

- *Anti-adhesive (elastic adhesive tape group) to remove residual glue.*
- *Duoderm ® or other dressings used in curative treatment in case of lesions.*
- *Cavilon ™ type skin protection film.*

As these treatments are prescribed within the scope of their indications, any AEs for them are described in the respective summary of product characteristics (SPC)s, which serve as a reference.

-

*To the procedures performed, methods/techniques used for the purpose of the research:*

NA

- List of AEs related to the studied disease (death due to the disease, relapse, ...):

The patients included will be patients hospitalized in the intensive care unit, most often with multiple pathologies, who are intubated and put on invasive mechanical ventilation.

The potential complications of intensive care management of the study patients are identical to those expected in the non-study population, including, but not limited to, nosocomial infections, complications of intubation procedures, anesthesia drugs, consequences of prolonged bed rest, occurrence of shock with a risk of multi-visceral failure, and death.

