These adverse events will be considered to be related to the disease being studied and not to the medical device being studied or to the investigative procedure.

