## **5.3. *ROLE OF THE INVESTIGATOR***

The investigator is responsible for the registration via an entry in the e-CRF:

- Any **serious and non-serious adverse events** that **may be related to the preceding investigation procedure**
- **Serious and non-serious incidents** (or risks of incidents) that may be related to the MD
- Events of interest (section 5.2 of the protocol)
- Special situations even in the absence of complications and severity criteria
- New Facts

For each adverse event recorded on the e-CRF, the investigator will make an independent assessment of severity (intensity), causality and seriousness.

The investigator will seek information about adverse events at each encounter with the patient.

The investigator will seek, whenever possible, to provide the definitive medical diagnosis.

All adverse events, whether reported by the patient or noted by study personnel, will be noted in the patient's medical record.

Exception: Peri-oral skin and mucosal lesions related to the fixation system are not to be collected in the CRF adverse event table. They are already included in the CRF follow-up pages. Other lesions outside of this area should be entered in the CRF adverse events page.

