### 5.3.2. Evaluation of the causality of adverse events

The investigator should use his or her knowledge of the patient, the circumstances surrounding the event, and an assessment of any other potential causes to determine whether the adverse event is considered to be related to the study MD or the investigative procedure.

The following guidelines should be considered:

- Temporal relationship between the onset of the event and the first use of the MD under study

- Course of the event, with particular attention to the effects of discontinuing the study MD or reintroducing the study MD (if applicable)
- Known mechanism of action at the MD
- Body site or organ that may or may not be affected by the MD or condition
- Known association of the event with the investigational MD or similar devices
- Known association of the event with the disease under study
- Presence of risk factors in the patient or use of concomitant medications known to increase the frequency of the event
- Presence of factors unrelated to the MD that are known to be associated with the occurrence of the event.

Causality of MDs according to MDCG 2020-10/1 page 9

|             |                                                                                                                                                                                                                                                                                                                                                         |
|-------------|---------------------------------------------------------------------------------------------------------------------------------------------------------------------------------------------------------------------------------------------------------------------------------------------------------------------------------------------------------|
| Not related | Causality with the MD, comparator or procedures can be excluded                                                                                                                                                                                                                                                                                         |

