| Possible    | Causality with the use of the MD, comparator, or CI procedures is weak but cannot be completely ruled out. Other causes are also possible (underlying or concomitant disease/clinical condition/effect of another treatment). Cases where the relationship cannot be assessed or no information has been obtained should also be classified as possible |
| Probable    | The causal link to the use of the MD or comparator, or the relationship to the CI procedures, appears relevant and/or the event cannot be reasonably explained by another cause                                                                                                                                                                         |
| Some        | The serious adverse event is related to the use of the MD, comparator, or trial procedures beyond a reasonable doubt.                                                                                                                                                                                                                                   |

The categories "possible", "probable" and "certain" correspond to a proven or reasonably foreseeable causal link.

In cases where no information is available to define the causal link, fill in

The default setting is "possible".

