### 5.3.4. Procedures and deadlines for notifying the sponsor

The investigator notifies the sponsor of events as defined below:

| TYPE OF EVENT                                                                                       | METHODS OF NOTIFICATION                                                                                           | NOTIFICATION DEADLINE                                                                                                      |
|-----------------------------------------------------------------------------------------------------|-------------------------------------------------------------------------------------------------------------------|----------------------------------------------------------------------------------------------------------------------------|
| Event of interest                                                                            | Collection in the e-CRF (AE table)                                                                                | Without delay
as soon as you are aware of it,
and at the latest within 3 calendar days                 |
| Non-serious adverse event Suspected of being related to the clinical investigation procedure | Collection in the e-CRF (AE table)                                                                                | As soon as you are aware of it                                                                                             |
| Serious adverse event Suspected of being related to the clinical investigation procedure     | Collection in the e-CRF (AE table)
+ Initial SAE form
+ Follow up if necessary
By mail                   | Without delay to the Sponsor,
as soon as you are aware of it,
and at the latest within 3 calendar days |
| New Fact                                                                                     | By email                                                                                                          | Without delay to the Sponsor,
as soon as you are aware of it,
and at the latest within 3 calendar days |

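### Section 5.2.2 classes ventilator-associated pneumonia both as related and as not related to the fixation procedure, and loose wording nearby leaves room for attribution before events of interest are entered

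*Protocol*

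**What the plan says.** **Attribution (5.2.2).** Among the adverse events expected from the investigation procedure, the protocol names unscheduled extubations, tracheal complications including laryngeal dyspnoea, and ventilator-associated pneumonia. Further down, the same section describes the complications of intensive care, "including, but not limited to, nosocomial infections, complications of intubation procedures" and others. It closes with a ruling: "These adverse events will be considered to be related to the disease being studied and not to the medical device being studied". That sentence goes on to exclude the investigation procedure as well. No exception is made for the events named earlier in the section.

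**Entry into the eCRF.** Section 5.2.3 says that events of interest "induced by these MDs will be collected" and then names three: self-extubation, laryngotracheal dyspnoea and ventilator-associated pneumonia. The safety row of the schedule table in section 4.3 reads "Collection of adverse events related to the investigation procedure and incidents related to the MD"; no row covers events of interest as such. Section 5.3, by contrast, makes events of interest a separate item for eCRF entry, and the notification table in 5.3.4 gives them their own row ("Event of interest") with a deadline of 3 calendar days. Neither of these carries a relatedness condition, although neighbouring items do.

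**Causality and declaration.** Under 5.3.2 an event is not related only if "Causality with the MD, comparator or procedures can be excluded". It is possible if the link "is weak but cannot be completely ruled out". Under 5.4.2 serious events classed possible, probable or certain are declared to the authority, and only the unrelated class is left out.

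**The concern.** An investigator facing a ventilator-associated pneumonia finds two instructions in one section. One says that it is an expected event of the fixation procedure. The other says that, as a nosocomial infection, it is due to the disease. The class chosen decides whether a serious case is declared, so the conflict has a practical consequence.

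The second issue is which cases reach the database. Section 4.1 describes an open study, and blinded review is described only for the lesion photographs. If staff take the causal phrase in 5.2.3 or the schedule row as a filter, they judge cause knowing the fixation and before anything is recorded. Cases left out in this way cannot be recovered at analysis.

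Self-extubation is less exposed, because sections 2.2.2 and 6.2.1 count it as a secondary endpoint without attribution.

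**Working it through.** **1. Pneumonia under both rules of 5.2.2.** Pneumonia acquired on the ventilator is a nosocomial infection. The list of procedure events makes it related; the closing ruling makes it unrelated to device and procedure. The conflict is direct.

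**2. Laryngeal dyspnoea.** Section 5.2.1 limits the investigation procedure to placing, maintaining, changing and removing the fixation. Intubation lies outside it. If dyspnoea counts as a complication of intubation, the closing ruling applies and the same conflict follows. That is one inference, and a reasonable one.

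**3. Consequence for a serious pneumonia.**
- Judged case by case under 5.3.2: a weak link that cannot be ruled out is possible, so 5.4.2 requires declaration.
- Judged by the closing ruling of 5.2.2: not related, so no declaration.

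The same case has two outcomes, depending on which sentence is followed.

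**4. Entry rules side by side.**

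| Place | Condition for entering an event of interest |
|---|---|
| 5.3, list of items to register | none |
| 5.3.4, notification table | none |
| 5.3, causality assessment | made on events already recorded |
| 5.2.3 | causal phrase, followed by a named list |
| 4.3, schedule row | related events and device incidents only |

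The first three rows agree and give a workable rule: enter every case, then assess causality. The last two permit a narrower reading but do not require it.

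**5. Illustrative size of a narrow reading of the entry rule.** The documents give no rate for pneumonia and no recording rate, so both are assumed here. From 6.2.2: 16 centres × 24 patients = 384 per fixation, and 2 × 384 = 768 in total.
- *Equal under-recording in both arms.* Missed cases = 768 × p × (1 − r), with true rate p and recorded share r. For p = 0.10: 15.4 (r = 0.8) to 30.7 (r = 0.6). For p = 0.20: 30.7 to 61.4. The risk ratio does not change: a true 15% against 10% appears as 12% against 8% (r = 0.8) or 9% against 6% (r = 0.6), a ratio of 1.5 each time.
- *Recording that differs by device within a centre by g.* False difference = p × g. For g = 0.10 to 0.20 and p = 0.10 to 0.20 this is 1 to 4 percentage points.
- *Comparison with noise.* The 95% half-width of the difference with all cases recorded is t(0.975, 14) × √(2p(1−p) × [ICC/2 + (1−ICC)/24] / 16). At the plan's ICC of 0.10, with half of it between periods, it is 6.7 points (p = 0.10) and 9.0 points (p = 0.20). At an assumed ICC of 0.01 it is 4.9 and 6.5 points. The recording gap needed to exceed it, half-width / p, runs from 33 to 67 percentage points.

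Under these assumptions, a narrow reading costs completeness and would not by itself produce an apparent device difference beyond sampling error.

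**The case against.** The other side has a good case.

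- A specific listing normally prevails over a general class. The closing ruling of 5.2.2 concerns complications of intensive care that patients outside the study would have as well, so the named events can be read as outside it. The scale in 5.3.2 also pulls doubtful cases towards possible.
- The entry rule is clear where it operates, in 5.3 and 5.3.4. A separate category for events of interest would be nearly redundant if only attributed cases counted. Section 5.4.1 has the sponsor record, with no causal condition, events that the protocol defines as critical to evaluating the outcome. Section 5.2.3 reads naturally as a label on a closed list.
- A pneumonia entered as an event of interest still reaches the sponsor, who makes its own causality assessment of serious adverse events under 5.4.1.
- Neither pneumonia nor dyspnoea is an endpoint, and no comparative test of them is planned.

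Most of this stands for entry: the causal phrase and the schedule row are loose wording, not a competing rule. It does not remove the attribution conflict. The text does not say which sentence of 5.2.2 prevails, and the closing ruling assigns cause by class, which displaces the case-by-case judgement of 5.3.2. Nor can the causality scale recover a case that was never entered.

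**Conclusion.** On attribution, 5.2.2 is wrong as written: directly for ventilator-associated pneumonia, and by one inference for laryngeal dyspnoea. On entry, 5.2.3 and the schedule row are loosely worded against a sound rule in 5.3 and 5.3.4. The point is minor. It touches the completeness of descriptive safety counts and the causality class of serious cases. The primary and secondary endpoints and the sample size are unaffected. The figures for missed cases rest on assumed event and recording rates.

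A reader might infer more, and the documents do not support it:

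- *That only attributed cases are to be entered.* The operative sections set no such condition.
- *That the device comparison of these harms is biased.* Every centre uses both fixations, so a centre that reads the rule narrowly throughout mainly undercounts both arms. Bias would require attribution to differ by device within centres, and nothing indicates a direction or size.
- *That first-period cases have been lost.* Nothing shows that any centre entered only attributed cases.
- *That the safety committee cannot learn of these events.* Its own list in 5.6 is self-extubation and repositioning, but it also receives safety information sent to the authorities and may meet at the sponsor's request on problems that investigators report.

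**What to change.** 1. In 5.2.3, replace the causal phrase with a rule such as: *Every self-extubation, laryngotracheal dyspnoea and ventilator-associated pneumonia during the period defined in 5.3.5 is entered in the eCRF, whatever its presumed cause.*
2. After the closing ruling of 5.2.2, add: *This does not apply to the events named in 5.2.3; their causality is judged case by case under 5.3.2.*
3. Add events of interest to the safety row of the schedule in 4.3.

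No retrospective check of first-period records is needed unless a centre is found to have entered only attributed cases.

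The cost is three short edits, using the existing adverse-event table, and some additional entries. At an assumed pneumonia rate of 10 to 20%, there would be at most 768 × 0.10 = 77 to 768 × 0.20 = 154 pneumonias in all, or about 5 to 10 per centre over both periods (divided by 16). The number of additional entries is smaller if centres already enter every case. Diagnosis remains unblinded; only the opening for attribution before entry is closed.

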### **5.2.4. Non-serious adverse events not subject to registration**

Complications due to concomitant treatments, which are therefore not imposed by the protocol, cannot be considered as events related to the MD, the comparator or the investigation procedure and will therefore not be entered in the eCRF. They must be transmitted to the regional pharmacovigilance center (CRPV).

Complications related to routine procedures (diagnostic or therapeutic) implemented as part of the patient's usual management outside of the CI protocol cannot be considered as events related to the MD, comparator or investigative procedure and will therefore not be entered into the eCRF. They must also be transmitted to the regional pharmacovigilance center.

### **5.2.5. Serious Adverse Event not submitted to registration and notification to the sponsor**

Some circumstances requiring hospitalization do not fall under the severity criterion "hospitalization/extension of patient's hospitalization" and should not be recorded in the eCRF and notified to the sponsor as SAE :

- Hospitalization for medical or surgical treatment scheduled before the beginning of the research or usually performed and concerning a previously known pathology not related to the research and not associated with a deterioration of the patient's condition (e.g.: change of catheter, probe, implantable chamber, extraction of wisdom teeth, etc.).

## **5.3. *ROLE OF THE INVESTIGATOR***

The investigator is responsible for the registration via an entry in the e-CRF:

- Any **serious and non-serious adverse events** that **may be related to the preceding investigation procedure**
- **Serious and non-serious incidents** (or risks of incidents) that may be related to the MD
- Events of interest (section 5.2 of the protocol)
- Special situations even in the absence of complications and severity criteria
- New Facts

For each adverse event recorded on the e-CRF, the investigator will make an independent assessment of severity (intensity), causality and seriousness.

The investigator will seek information about adverse events at each encounter with the patient.

The investigator will seek, whenever possible, to provide the definitive medical diagnosis.

All adverse events, whether reported by the patient or noted by study personnel, will be noted in the patient's medical record.

Exception: Peri-oral skin and mucosal lesions related to the fixation system are not to be collected in the CRF adverse event table. They are already included in the CRF follow-up pages. Other lesions outside of this area should be entered in the CRF adverse events page.

### 5.3.1. Assessment of the intensity of adverse events

The Common Terminology Criteria for Adverse Events (CTCAE) version 5, Nov. 2017 will be used to assess the intensity of adverse events.

The table below will be used to assess the intensity of adverse events that are not specifically listed in the CTCAE.

| Grade | Intensity                                                                                                                                                                                          |
|-------|----------------------------------------------------------------------------------------------------------------------------------------------------------------------------------------------------|
| 1     | Mild; asymptomatic or mild symptoms; clinical observations or diagnostic only                                                                                                                      |
| 2     | Moderate; minimal, local or non-invasive intervention indicated; or limitation age-appropriate instrumental activities of daily living a                                                |
| 3     | Severe or medically significant, but not immediately life-threatening; hospitalization or extension of hospitalization indicated; disabling; or limiting activities of daily living b,c |
| 4     | Life-threatening consequences or urgent intervention indicated c                                                                                                                        |
| 5     | Deaths related to an adverse event c                                                                                                                                                    |

a Instrumental activities of daily living refer to preparing meals, shopping or buying clothes, using the telephone, managing money, etc.

b Examples of personal care activities of daily living include bathing, dressing and undressing, eating, using the toilet, and taking medications as performed by patients who are not bedridden.

c **Grade events likely to be assessed as "significant medical event", and grade 4 and 5 events should be reported as serious adverse events.**

